### Inclusion and exclusion criteria

The predefined inclusion and exclusion criteria used to determine study eligibility are summarized in Table 1.

**Table 1 pone.0357117.t001:** Inclusion and exclusion criteria.

	Inclusion criteria	Exclusion criteria
Patient Level	• Age ≥ 18 years • At least one life-limiting chronic condition reflected by at least two billings of the German chronic care fee (“Chronikerpauschale”, EBM GOP 03220/03221 or equivalent under selective contract) in two of the four quarters preceding study enrolment • Continuous treatment in the participating practice for at least four quarters prior to inclusion • Patients in an unstable phase of chronic disease with ASE related to their chronic condition and/or hospitalizations due to their chronic condition within the past three years • Patients in a stable phase of chronic disease with at least one sign of a high risk of decompensation*	• Estimated life expectancy based on the assessment of the treating GP at the start of the intervention of less than one year (minimum intervention period)
Practice Level	• Practices providing routine care as GPs in the federal state of Baden-Württemberg, Germany • Employment of a nursing professional	• Participation in similar studies

*The risk of decompensation was based on the clinical judgement of the participating GPs in regard of the following aspects: presence of multimorbidity with geriatric characteristics (e.g., immobility, cognitive impairment, or frailty), unfavorable living circumstances (e.g., living alone, partner requiring care, absence of nearby relatives), long-term care dependency (Pflegegrad, care level), frequent changes/dose adaptions in medication, increasing frequency of acute exacerbations or clinically relevant deterioration in vital parameters (e.g., blood pressure, pulse, oxygen saturation, change in weight) indicating disease progression, and reduced ability to participate in or adhere to the care processes.

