### Setting

The trial is conducted in the German ambulatory primary care setting, namely in 20 general practices located in the federal state of Baden-Württemberg, Germany. The participating practices provide routine outpatient care services within the German statutory health insurance (SHI) system.

The target population of PRIMA are patients with a chronic condition as defined within the German statutory healthcare system. Within this system, a chronic condition can be identified on the Uniform Value Scale (EBM), which is jointly developed by the National Association of SHI Physicians and the National Association of SHI Funds. The conceptual basis of this definition is derived from German social law, in particular the definition of “severe chronic disease” according to § 62 of the Social Code Book V, and its specification by the Federal Joint Committee [20]. Within the EBM framework, chronic illness is operationalized for billing purposes in the billing code chronic care reimbursement (“Chronikerpauschale”: 03220/03221) [21]. Patients are classified as chronically ill if they have a documented, continuous need for medical care due to the same confirmed diagnosis over a period of at least 12 months. This requirement is typically operationalized through repeated physician–patient contacts across multiple quarters rather than pre-defined clinical criteria, usually in at least three out of four consecutive quarters, reflecting sustained utilization of care. In addition, an ongoing need for treatment must be present. Thus, the EBM-based definition represents an administrative and utilization-based proxy for chronic illness, grounded in legal and regulatory frameworks rather than purely epidemiological or clinical definitions. Patients eligible for inclusion in the study were identified from the population of individuals receiving the chronic care reimbursement billing code (“Chronikerpauschale”), which served as the source population for the study. Additional clinical eligibility criteria were subsequently applied to identify patients with an increased risk of care instability or decompensation in a step-wise approach.

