### Recruitment

#### Intervention group – participating practices, PNs and patients.

Participating practices were recruited between January and December 2025, while information about the PRIMA project had already been shared in the two months leading up to the project start. Recruitment was conducted by the Association of SHI Physicians of Baden-Württemberg (KVBW) through two sequential steps. First, postal letters were sent to a sample of randomly selected practices, followed by information and outreach via email to a further randomly selected sample of practices in the federal state of Baden-Württemberg, Germany. PNs employed in PRIMA were recruited by the practices themselves or via the KVBW. All PNs participating in PRIMA must have completed a three-year vocational training program as nursing professional (*Altenpfleger:in*, *Gesundheits- und Krankenpfleger:in* or *Pflegefachfrau/-mann*) and possess either an academic postgraduate qualification in nursing or at least five years of professional experience in nursing, preferably across different care settings. Alternatively, nurses who have obtained an academic qualification in nursing, such as a bachelor’s or master’s degree with a specialization in Advanced Nursing Practice could be employed. Patients eligible for participation were identified in a stepwise approach using a combined data-driven approach and clinical judgement by the GP and the respective practice team based on the inclusion and exclusion criteria. All study participants are recruited between 1 January 2026 and 30 September 2026. Eligible patients are informed about the study during routine consultations. Written informed consent is obtained by the treating GP and forwarded to KVBW prior to participation using a standardized consent form approved by the ethics committee. Where applicable, consent must be provided by a legal guardian or authorized representative.

For the PE, all study participants with the capacity to provide informed consent are invited by the PN to participate in the surveys of the PE. Recruitment of the practice teams, patients as well as their relatives and collaborators for the qualitative case studies is guided by the scientists from Institute of General Practice and Interprofessional Care, Tuebingen (IAIV) in a selective sampling approach guided by the principle of information power. Informed consent was obtained from all participants in the PE [25].

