### Control group – patients and practices

The CG consists of matched patients receiving usual care in comparable general practices outside the PRIMA intervention. Patients will be identified using routine data from the KVBW and AOK Baden-Württemberg (AOK BW) databases and matched to participants in the IG at both patient and practice level. Matching criteria include demographic and clinical characteristics such as age, sex, diagnosis, and comorbidities to ensure comparability between groups. Usual care reflects standard ambulatory primary care within the German statutory healthcare system as delivered by GPs outside the PRIMA intervention. This allows a pragmatic and policy-relevant evaluation of the intervention under real-world conditions, assessing the added value of the PRIMA care model compared to standard practice without altering routine care pathways. There is no control group for the PE.

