**Secondary outcomes – KVBW data**				
Micro	ASE per person-year	ASE rate adjusted for patient-specific observation time	KVBW	Intervention period
Micro	Patients with ≥1 ASE	Proportion of patients with at least one ASE	KVBW	12 months
Micro	Ambulatory emergencies	All emergency contacts independent of diagnosis	KVBW	12 months
Micro	Ambulatory emergencies per person-year	Rate-adjusted emergency contacts	KVBW	Intervention period
Micro	GP utilization	Number of GP contacts / quarters with GP visits	KVBW	Intervention period
Micro	Specialist utilization	Number of specialist contacts / quarters	KVBW	Intervention period
Meso	Treatment intensity	EBM points per patient and per practice	KVBW	Intervention period
Meso	Continuity of care	Continuity-of-Care Index (e.g., Bice–Boxerman)	KVBW	Intervention period
Meso	Care coordination	Number of providers; referral-based specialist visits	KVBW	Intervention period
Micro	Preventive care	Vaccination rates (influenza, pneumococcal, COVID-19)	KVBW	Intervention period
Macro	Outpatient costs	Cumulative outpatient costs incl. intervention costs	KVBW	12 months
Macro	Outpatient cost-effectiveness	Cost per outcome achieved	KVBW	12 months

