### Statistical analysis

#### Matching.

The analysis population comprises patients enrolled in the intervention practices and matched CGs identified from routine data of the Association of SHI Physicians Baden-Württemberg (KVBW) and AOK BW, respectively.

First, matching variables associated with treatment allocation and study outcomes will be defined based on a literature review and expert consultation [28]. Patient-level variables will include sociodemographic and clinical characteristics such as age, sex, and the number of ASE in the pre-observation period. Practice-level variables will include structural characteristics such as practice type and size, approximated by level of care provision or the number of physicians per practice. Additionally, regional indicators such as the density of doctors or the average distance to the nearest GP are considered.

Second, suitable matching methods will be evaluated regarding methodological appropriateness and feasibility using routine data. Given the multilevel structure of the intervention, several approaches will be considered, including Propensity Score Matching, Coarsened Exact Matching, Optimal Full Matching, and cluster-based matching approaches for observational studies [29–32].

Matching will be conducted separately for the two data sources: KV data will be matched at TUM, while AOK BW data will be matched directly by AOK BW. The resulting matched datasets will be assessed for covariate balance and comparability between intervention and CG [33]. The preferred matching approach will be the method achieving the best balance across predefined matching variables and thereby minimizing selection bias.

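### Controls have no stated counterpart to the four-quarter practice-attachment criterion and no index date, so the continuity, provider-count and GP-contact comparisons are open to selection bias of uncertain direction

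*Protocol article*

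**What the plan says.** The section on inclusion and exclusion criteria introduces Table 1 with "The predefined inclusion and exclusion criteria used to determine study eligibility are summarized in Table 1". One patient-level criterion is "Continuous treatment in the participating practice for at least four quarters prior to inclusion". The recruitment section adds the route of entry for the intervention group: "Eligible patients are informed about the study during routine consultations", with consent taken by the treating GP between January and September 2026.

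Controls are patients in comparable practices outside PRIMA, found in routine data. Under the control-group heading, "Matching criteria include demographic and clinical characteristics such as age, sex, diagnosis, and comorbidities to ensure comparability between groups". The Matching subsection says: "Patient-level variables will include sociodemographic and clinical characteristics such as age, sex, and the number of ASE in the pre-observation period". It adds practice variables (type, size) and regional indicators, states that the variables are still to be defined from literature and expert advice, and prefers the method that best balances the predefined variables. The Data section leaves the KVBW control criteria to the evaluator.

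Table 2 lists a continuity-of-care index (Bice–Boxerman is the example given), the number of providers and the number of GP contacts as secondary outcomes from KVBW data over the intervention period.

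**The concern.** The attachment criterion selects intervention patients on the pre-period level of something on which they are later compared. Past attachment to one practice predicts future attachment, and regular contact predicts more contact. If the control pool includes people who change or split practices, or who are not in contact when follow-up starts, the groups will differ on these outcomes even with no intervention effect. Best balance on predefined variables does not help with a variable that was not predefined.

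The matching plan handles this for the primary outcome, because prior ASE is a named variable. It names no pre-period counterpart for continuity, provider count or GP contacts. Enrolment is also staggered over nine months, so controls need a time zero, and none is given.

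The Discussion treats fewer ASE as a proxy for better continuity. A continuity result distorted by selection could therefore be misread as evidence about the mechanism.

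**Working it through.** The plan gives no figure on this point to reproduce. The check has three parts.

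**1. Entry conditions side by side**

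| Condition | Intervention | Control |
|---|---|---|
| Chronic care fee population | Table 1; also the Setting section | Setting describes it for the whole study ("which served as the source population for the study") |
| Four quarters in one practice | Table 1, in the participating practice | None stated; as worded, a patient outside PRIMA cannot meet it |
| Contact at entry | By recruitment route | None stated |
| Index date | Enrolment, January to September 2026 | None stated |
| Pre-period ASE | Matching variable | Matching variable |
| Pre-period continuity, providers, GP contacts | Not named | Not named |

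The matching lists give examples only, but within sociodemographic and clinical characteristics. Practice attachment and an index contact are neither.

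**2. Size on the index the plan names**

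Bice–Boxerman index = (Σnⱼ² − N) / (N(N − 1)), where nⱼ is the number of contacts with provider j and N the total. Assume four contacts a year.

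- All with one practice: (16 − 4)/12 = 1.00.
- Split 2/2: (4 + 4 − 4)/12 = 0.33.
- Difference: 0.667.
- If 10% of controls split this way, the control mean is 0.10 × 0.667 = 0.067 lower; at 20% it is 0.20 × 0.667 = 0.133 lower.

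The document gives neither the share nor the contact pattern. Both are assumptions.

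**3. Direction: simulation with no treatment effect**

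Assumptions: 200,000 patients; on average 1.2 GP contacts per quarter, varying between patients; 75% of these with the own practice (90% in the high-loyalty case); three specialists with 0.8 contacts per quarter in total; outcomes over four quarters. The intervention group needs contacts in two of four prior quarters, own-practice contact in all four, and a contact in the nine-month window. Controls need only the first.

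| Scenario | Index, intervention vs control | Gap | Providers, intervention vs control |
|---|---|---|---|
| Equal risk mix | 0.388 vs 0.310 | +0.078 | 3.66 vs 3.52 |
| Equal risk mix, high loyalty | 0.447 vs 0.370 | +0.077 | 3.44 vs 3.30 |
| Mildest unequal risk selection | 0.322 vs 0.293 | +0.029 | 4.13 vs 3.72 |
| Strongest unequal risk selection | 0.271 vs 0.359 | −0.088 | 4.25 vs 3.45 |

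In the last two rows the intervention group is enriched for high-risk patients with more specialist use and the controls are not.

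Applying the same conditions to controls at equal risk mix brings both gaps to zero (0.388 vs 0.388; 3.66 vs 3.66). Under unequal risk selection the filter alone does not: the index gap is 0.322 − 0.359 = −0.037 in the mildest case and 0.271 − 0.419 = −0.148 in the strongest. The filter removes the attachment selection, not the risk selection.

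**Feasibility.** KVBW data start on 1 January 2024, eight quarters before the first possible enrolment. The four quarters before any index quarter are therefore covered.

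**The case against.** The strongest reply is that this is silence in a condensed article. Table 1 is headed as study eligibility, the chronic-fee population is described for the study as a whole, the matching lists are open, the variables are to be those related to allocation and outcome (prior attachment would qualify), and the evaluator sets the KVBW criteria. This stands in part: a reader might infer that controls are exempt from Table 1, and the document does not say so. But the attachment criterion refers to the participating practice and cannot carry over to controls as worded. Who may be a control, and from when, is a matter of design.

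A reader might also infer that selection favours the intervention on both continuity and coordination. The check does not support that: the intervention group has more providers in every scenario, and the continuity gap can change sign. Nor is attendance at a consultation an eligibility criterion; it is the recruitment route, although it still conditions entry on contact.

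A third tempting inference is that the primary endpoint is biased. Nothing computed here shows it. Prior ASE is a matching variable, baseline differences are examined, and relevant covariates enter the adjusted models.

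The limitations paragraph acknowledges residual differences after matching, but ties them to which routine variables are available and how matching is done. Here the relevant data have largely been requested already.

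**Conclusion.** The point holds in limited form. The article selects intervention patients on four quarters of attachment to one practice and recruits them through contact with it. It states no counterpart for controls, no index date, and no pre-period value of the three outcomes most affected. At equal risk mix the continuity index would be biased towards the intervention, by about 0.08 in the simulation or 0.067 to 0.133 in the simple illustration. Once unequal risk selection is allowed for, the simulated gap runs from +0.03 to −0.09, with 0.4 to 0.8 more providers in the intervention group. These sizes rest on assumed contact rates, loyalty and specialist use, since the document gives none. They show that the bias is plausible and not negligible, not how large it is in this trial. No separate figure was calculated for GP contacts. The exposure is confined to secondary outcomes. It should be corrected before matching is fixed.

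**What to change.** 1. Before matching, restrict the control pool to patients who meet the claims-computable Table 1 criteria in their own practice: age at least 18; the chronic care fee, or its selective-contract equivalent where visible, in two of the four quarters before index; and claims from the same practice across those four quarters. Apply this to controls only. Filtering the intervention group could drop enrolled patients and conflict with the intention-to-treat definition.
2. Assign each control the index quarter of its matched intervention patient and require a contact with the control's practice in that quarter.
3. For continuity, number of providers and GP contacts, match on or adjust for the pre-index value of the same measure. The filter must accompany the risk matching, not replace it.
4. Give AOK BW the same eligibility and index rule before it builds its own matched dataset. This does nothing for the three KVBW outcomes above, but keeps the control definition the same in both sources.

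The cost is a short addition to the matching specification, using data already requested, and a smaller control pool. How much smaller is unknown: in the simulation 31,681 of 149,801 (21%) or 42,267 of 149,737 (28%) of the code-only pool met the conditions, which depends heavily on the assumed contact rate. The remaining pool should be counted against the planned 20 × 112 = 2,240 intervention patients. Selective-contract patients may be incompletely visible in KVBW claims, since participation in GP-centred care is collected on a consent form described only for the intervention group. A sensitivity analysis should examine this.

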
**Fig 2 pone.0357117.g002:**
[figure not shown]
New care model in PRIMA.

Participating practices are offered the optional use of SmED (Strukturierte medizinische Ersteinschätzung in Deutschland, structured medical initial assessment tool), a structured software tool for medical initial assessment. SmED supports urgency assessment and facilitates allocation of patients to the most appropriate professional within the practice team.

Participants in the PRIMA study may receive any concomitant care as part of routine healthcare within the German statutory healthcare system. The intervention is delivered as part of routine primary care in participating practices and does not interfere with or restrict other aspects of patients’ healthcare utilization.

As the PRIMA intervention is an organizational care model implemented at practice level, adherence is primarily supported through structured training of participating practice teams, and PNs especially, provision of implementation support, and continuous contact with the study coordination team. No specific adherence measures are applicable for comparator patients, as the CG is based on routine data reflecting usual care without active participation requirements.

Participants will remain in the analysis population unless they withdraw consent or data availability ceases. In case of death, participants are retained in the intention-to-treat (ITT) population, and data are included up to the time of death. As the PRIMA intervention is implemented at the practice level as an organizational care model, no individual-level modification of the intervention is foreseen. Practices may discontinue participation in the intervention in case of organizational changes. However, no modifications of the intervention at individual patient level are planned.

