#### Effectiveness evaluation.

The primary endpoint (number of ASE after 12 months) will be analyzed according to the ITT principle. The ITT population of the IG comprises all patients enrolled in the NCM by the end of the nine-month recruitment period, receiving at least 12 months of care. The smallest unit of analysis is the individual patient, as outcomes are assessed at patient level. In a baseline analysis, sociodemographic and clinical characteristics of the IG will be compared with those of the matched CG to assess the effectiveness of the matching procedure and identify potential determinants of the study endpoints [34,35]. The significance of the differences will be tested using linear mixed models for continuous variables with normal distribution, logistic models for binary variables, and the chi-square test and Fisher’s test for categorical variables. Subsequently, the rate of ASE in the IG and CG will be analyzed using multi-level regression models with patients nested within practices to account for the hierarchical structure of the data [36]. As a sensitivity analysis, models with cluster-robust standard errors at the practice level will be estimated. Relevant covariates identified in the initial analyses will be included in adjusted regression models [37].

Continuous secondary endpoints, including healthcare costs, will be analyzed using adjusted mixed linear models. Mortality will be assessed using survival analyses, while binary outcomes will be analyzed using generalized linear mixed models. Covariates will be selected analogously to the primary analysis. Extensive sensitivity analyses are planned to assess the robustness of the evaluation parameters. The choice between matched datasets derived from KVBW or AOK-BW routine data will depend on the respective endpoint as specified in Table 2. Statistical significance will be defined as a two-sided p-value <0.05. Where relevant, 95% confidence intervals are provided.

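### The GP's under-one-year prognosis exclusion is not mirrored in the claims-based controls; by itself this biases survival towards the new model and may bias costs and ASE

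*Protocol article*

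**What the plan says.** Protocol article, Inclusion and exclusion criteria (Table 1): the sole exclusion at patient level is "Estimated life expectancy based on the assessment of the treating GP at the start of the intervention of less than one year".

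Recruitment, intervention group: eligible patients are "identified in a stepwise approach using a combined data-driven approach and clinical judgement by the GP and the respective practice team", so the treating practice is in a position to apply this exclusion.

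Control group – patients and practices: "Patients will be identified using routine data from the KVBW and AOK Baden-Württemberg (AOK BW) databases". The section on the PRIMA intervention adds that "the CG is based on routine data reflecting usual care without active participation requirements".

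Matching variables are named in two places. The control-group section says "Matching criteria include demographic and clinical characteristics such as age, sex, diagnosis, and comorbidities to ensure comparability between groups". The Matching section names patient-level variables "such as age, sex, and the number of ASE in the pre-observation period", plus practice structure and regional indicators. Both lists are open-ended. AOK BW performs its own match before delivering data, and the two data sources are not linked.

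Outcomes (Table 2) and Effectiveness evaluation: overall survival and total healthcare costs come from AOK BW data only, and "Mortality will be assessed using survival analyses". Patients who die stay in the ITT population with data up to death.

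**The concern.** The exclusion rests on a clinical forecast that is made at enrolment and is not described for controls. Intervention patients expected to die within a year are screened out. A control with the same age, sex, diagnoses and prior ASE count, but in the last months of life, can stay in the pool. The Matching section sets its own standard: matching variables should be related both to receiving the intervention and to the outcomes. A rule that keeps patients out of the intervention because they are expected to die meets both conditions, yet no named variable represents it.

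Overall survival is most exposed, because the exclusion is itself a forecast of death. Total healthcare costs may be affected if spending rises near death, and ASE if emergencies cluster there. Timing matters for survival and total costs: AOK BW delivers a pre-matched data set, so a restriction not specified beforehand may be impossible to add later.

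**Working it through.** The plan gives no figure on this point, so there is nothing to reproduce. What follows is an illustration under no true effect. Every input is an assumption; the document supplies none of them.

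**Notation**
- p = share of matched controls who would have failed the GP criterion.
- d = their 12-month mortality; b = 12-month mortality of everyone else.
- m = their ASE rate relative to everyone else; e = fraction of the year for which they are observed. Everyone else is credited with a full year.

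**1. Survival.** Intervention mortality = b. Control mortality = (1 − p)·b + p·d. Spurious ratio = b divided by that.

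| b | p | d | Control mortality | Ratio |
|---|---|---|---|---|
| 5% | 2% | 40% | 0.98×0.05 + 0.02×0.40 = 0.057 | 0.88 |
| 5% | 8% | 60% | 0.92×0.05 + 0.08×0.60 = 0.094 | 0.53 |
| 8% | 2% | 70% | 0.98×0.08 + 0.02×0.70 = 0.092 | 0.87 |
| 5% | 5% | 70% | 0.95×0.05 + 0.05×0.70 = 0.082 | 0.61 |
| 3% | 10% | 70% | 0.90×0.03 + 0.10×0.70 = 0.097 | 0.31 |

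The ratio is below 1 whenever d > b. For this mechanism alone, the direction on survival is therefore fixed.

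**2. ASE counts over 12 months.** Spurious ratio = 1 / [(1 − p) + p·m·e].

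- Full year credited (e = 1): p = 2%, m = 2 gives 1/1.02 = 0.98; p = 8%, m = 3 gives 1/1.16 = 0.86.
- That is inconsistent with 40–60% of these patients dying. If deaths are spread evenly over the year, e = 1 − d/2 = 0.8 to 0.7. Then p = 8%, m = 3, e = 0.8 gives 1/(0.92 + 0.192) = 0.90, and p = 2%, m = 2, e = 0.7 gives 1/(0.98 + 0.028) = 0.99. The range becomes about 0.90–0.99.
- With earlier death (p = 5%, e = 0.5), m = 1, 2, 3, 4 gives 1.03, 1.00, 0.98, 0.95. The bias vanishes at m·e = 1 and reverses below it.
- Per person-year the ratio is [(1 − p) + p·e] / [(1 − p) + p·m·e]. At p = 8%, m = 3, e = 0.8 this is 0.984/1.112 = 0.88.

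**3. The opposing selection.** Under Table 1, stable patients enter only if the GP sees a high risk of decompensation. Let a share s of matched controls not be high risk in that sense, with r times the ASE rate: ratio = 1 / [(1 − s) + s·r].

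- s = 20%, r = 0.7: 1/0.94 = 1.06. s = 40%, r = 0.5: 1/0.80 = 1.25.
- Multiplied by the 0.976 from step 2 (p = 5%, m = 3, e = 0.5): 1.04 to 1.22. The net ASE bias can run against the intervention.

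**4. Costs.** The document gives no cost figures. For AOK BW total costs, bias towards the intervention is plausible if costs rise near death. For outpatient costs the sign is open. The selection in step 3 applies here too.

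**The case against.** A reader might infer that the exclusion tilts survival, costs and ASE alike towards the new model, and that the ASE tilt could reach the planned 15% reduction. The documents do not support that. A ratio of 0.86 appears only if controls who die are credited with a full year of emergencies. Prior ASE is a named matching variable, which removes part of the difference. Table 1 also selects for high decompensation risk, partly on features that claims may not hold, such as living circumstances or adherence. The sample size section itself expects a raised ASE rate because of clinical selection. This objection stands in full for ASE and costs. For survival it means that only this mechanism, not the net contrast, can be signed.

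Second, the matching lists are open and final variables are still to be chosen, so an end-of-life marker could yet be included; diagnosis and comorbidities already carry some prognostic information. Table 1 can also be read as covering the whole study, so it is an inference from the described procedures that the exclusion reaches only one arm. Control eligibility code lists may sit in a full protocol or SAP that is not shown. That limits the point to what the article describes. It does not remove it, because a GP's forecast cannot be applied to controls whom no GP assesses.

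Third, the limitations concede residual differences after matching, and sensitivity analyses for informative censoring are planned. Neither addresses a selection made at entry.

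A reader might also take the wording that ITT patients receive at least 12 months of care to mean that early deaths leave the intervention arm, enlarging the bias. The intervention section states that patients who die are retained, so the point does not rest on that reading.

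**Conclusion.** The point holds in limited form. As described, the only patient-level exclusion is a GP prognosis that is applied to intervention patients and has no counterpart in the controls. By itself it biases overall survival towards the new model. The illustrative null mortality ratio is about 0.5–0.9 for 2–8% of controls affected, 40–60% mortality among them and 5% elsewhere; harsher assumptions go as low as 0.31. These figures show scale and are not estimates for this trial.

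AOK BW total costs and ASE may be biased, but the document does not allow a net direction to be stated for either. The primary ASE comparison should not be described as biased in favour of the intervention on this ground. The change is worth making because survival and total costs are named outcomes, the mechanism is identifiable in advance, and the AOK BW match cannot easily be redone.

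**What to change.** Before both the KVBW match and the AOK BW pre-match, define one claims-based end-of-life marker, for example palliative-care billing codes or diagnoses recorded before the index date. Outpatient claims are held in both sources, so a marker built from them can be identical in each. Data start on 1 January 2024 and recruitment on 1 January 2026, which leaves at least two years of look-back.

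Remove marked patients from the control pool, or match exactly on the marker, and treat intervention patients by the same rule. Because the ITT set comprises all enrolled patients, report a sensitivity analysis that keeps every one of them. Exact matching sits more easily with that definition than removal does.

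Report intervention versus control mortality in the first 90 days as a diagnostic of residual prognostic imbalance, and interpret the survival and total-cost contrasts in its light. Table 2 lists mortality under AOK BW only, so this check belongs there. It should not be a pass/fail rule: an early difference could also reflect the opposing high-risk selection or the crisis-management part of the intervention.

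Cost: a code list agreed with both data holders, a little more analysis work, and possibly a few unmatched intervention patients. The marker will capture GP prognosis only in part, which is why the 90-day comparison is needed alongside it.
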